### **Controlled Pain Modulation (CPM)**

At baseline, at the end of the 8-week acupuncture treatment, and at week 12, all patients will undergo CPM testing to determine the effectiveness of their descending inhibitory pathway. We will use the above-mentioned TSA-II system to administer tonic heat pain as the “test stimulus” in the CPM protocol. Hand immersion in the water bath apparatus, a temperature controlled container, will serve as a conditioning stimulus. We will use Heto water bath for hand immersion as the conditioning stimulus. We will measure CPM using the parallel paradigm in which two identical noxious ‘test stimuli’ will be delivered before and simultaneously with a noxious ‘conditioning stimulus.’ The test stimulus is first applied to the dominant forearm to reach a pain rating of greater than 60 on a numeric pain scale of 0-100. Patients will be asked to rate the level of pain intensity of the test stimulus (pain60 temperature) every 10 seconds (overall 4 pain reports). After a 15-minute break, the non-dominant hand will be immersed in the cold water bath up to the wrist at 10°C for 60 seconds. During the last 30 seconds of this immersion, the test stimulus will be repeated, and the patient will again rate the level of pain intensity experienced. The CPM effect is calculated as the difference (last minus first) in the average pain scores of the 2 test stimuli. A negative value indicates efficient CPM. This paradigm of conditioned pain modulation is routinely used in pain research.

### **Insomnia Severity Index (ISI)**

We will use patient-reported insomnia severity as measured by the Insomnia Severity Index (ISI) as a secondary objective measure. The ISI is one of the few well-validated patient-reported outcome measures designed to specifically assess the impact on daytime functioning and the amount of associated distress. The ISI includes 7 items that are scored on a five-point scale ranging from 0 to 4 with higher scores representing more severe insomnia symptoms. The optimal cutoff scores are 0-7 (no clinically significant sleep difficulties, 8-14 (sleep difficulties warrant further investigation) and 15+ (presence of clinically significant insomnia). The ISI has demonstrated internal consistency, reliability, construct validity, specificity and sensitivity in a representative sample of 1670 cancer

patients. The ISI has established minimally important change values to ensure that the change is not only statistically, but also clinically, meaningful to patients. A reduction of eight points has been deemed to be clinically significant improvement. The ISI has been used in several insomnia trials in cancer survivors and has demonstrated sensitivity to change in response to intervention as well as discriminating effects between interventions. All groups will complete the questionnaire at baseline and weeks 8 and 12. (Appendix A)

### **Hospital Anxiety and Depression Scale (HADS)**

A 14-item, self-rated instrument for anxiety (7 items) and depression (7 items) symptoms in the past week and has been extensively used in people with cancer. Established cutoffs for the depression and anxiety scales are independent and are: 0–7 not significant; 8–10 subclinical; and 11–21 clinically significant depression/anxiety. All groups will complete the questionnaire at baseline and weeks 8 and 12. (Appendix A)

### **Brief Fatigue Inventory (BFI)**

The BFI has been shown to have good reliability and to correlate well with other measures of fatigue. The three items rate current level of fatigue, and worst and usual fatigue in the prior 24 hours. The BFI score is calculated from the mean of completed items. All groups will complete the questionnaire at baseline and weeks 8 and 12. (Appendix A)

## **9.0 TREATMENT/INTERVENTION PLAN**

Patients will be randomized to one of three treatment groups, detailed below. Acupuncture treatments will be given at the Integrative Medicine Outpatient Center on [name] and/or at MSK's Breast and Imaging Center ([name]) and/or at MSK's Brooklyn Infusion Center ([name]). Patients who choose to receive acupuncture treatments at a non-Manhattan location will need to come into Manhattan for baseline, week 8, and week 12 assessments. Each treatment session will be approximately 30 minutes in duration, 10 minutes to insert needles, 20 minutes to leave needles in. Patients will receive twice weekly treatment each week for the first two weeks, followed by six weekly treatments, for a total of ten treatments over eight weeks. Adverse effects related to the administration of acupuncture will be collected each week before and after each treatment by the acupuncturist or research study assistant. All Integrative Medicine Service acupuncturists are licensed, credentialed employees of MSK. In both groups, patients' eyes will be covered with patches so they cannot observe the treatment procedure. To improve incentive to join and stay in the study, we will unblind all patients at Week 12, and offer those randomized to the Sham and UC groups 8 sessions over 8 weeks of Acu (real) treatment. For acupuncture points, please refer to section 4.2.

**Acupuncture Group:** After disinfecting the skin with an alcohol swab, the acupuncturist will insert sterilized 0.16 mm x 15 mm disposable filiform acupuncture needles in the ear points; 0.25 mm x 40 mm needles of the same quality will be used on body points. The acupuncturist will insert needles 12.5 mm (0.5 inch) into the skin for body points and 2.0 mm for ear points. Needles will remain for 30 minutes after the patient indicates experiencing *de qi* sensation.

**Sham Acupuncture Group:** For the sham treatment, we will use a combination of non-acupuncture points and a non-insertion procedure from a previously validated placebo acupuncture method. Acupuncturists will tap an empty plastic needle guiding tube on the bony area next to each of the 8 real acupoints in the arm and leg (LI4, SJ5, LI11, ST40) to produce some discernible sensation and then immediately apply a needle with a piece of adhesive tape to the dermal surface, without needle insertion, for a total of 30 minutes

**UC group:** We will ask patients randomized to UC to come to our clinic three times during the study, at Baseline, Week 8, and Week 12 to undergo QST and CPM tests. We will ask them to complete all questionnaires (CIPN severity by 0-10 11-point numeric rating scale, FACT/GOG-Ntx-11, NPS) and their pain medication diary at these time points. Questionnaires at Week 4 can be completed over the phone.

## **10.0 EVALUATION DURING TREATMENT/INTERVENTION**

The study schema and study calendar are presented in Section 1.0., Figure 1 and Table 2, respectively. Validated patient-reported outcome questionnaires: Functional Assessment of Cancer Therapy/ Gynecologic Oncology Group-Neurotoxicity (FACT/GOG-Ntx) questionnaire, Neuropathy Pain Scale (NPS), and Numeric Rating Scale (NRS) for pain, tingling and numbness will be assessed at baseline, and weeks 4, 8, and 12 for the acupuncture and sham acupuncture groups. The Treatment Expectancy Scale (TES) will be completed at baseline, weeks 4, 8, and 12. The usual care control group will complete the questionnaires at baseline, and weeks 4, 8 and 12. CIPN severity will be assessed at baseline and weeks 8 and 12. The pain medication list will be collected at baseline, and weeks 4, 8, and 12. Both the quantitative sensory testing and Controlled Pain Modulation (CPM) will occur at baseline (+ 1 week), at the end of the 8-week treatment phase (+/-3 days), and at 12 weeks (+/-3days). All groups will complete the Insomnia Severity Index (ISI), Hospital Anxiety and Depression Scale (HADS), and Brief Fatigue Inventory (BFI) at baseline, and weeks 8 and 12. At the end of the study, patients in the true and sham acupuncture groups will complete the Study Allocation Belief Form, to guess which group they were assigned for evaluation of blinding to random assignment and why they believe that to be the case.

## **11.0 TOXICITIES/SIDE EFFECTS**

Patients will be monitored for side effects at each visit. Only adverse effects related to the administration of acupuncture will be collected each week by the acupuncturist or research study assistant.

Acupuncture is a generally safe treatment modality when performed by qualified practitioners. No serious adverse events were reported in our pilot study.

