| Study Allocation Belief                                                                                          |   |   |   | X |
| Pain Medication List                                                                                          | X | X | X | X |
| Safety Assessment                                                                                                | X | X | X |   |
| Quantitative Sensory Testing (QST)                                                                               | X |   | X | X |
| Controlled Pain Modulation (CPM)                                                                                 | X |   | X | X |

1. In the case of any missed sessions during the study, the testing, questionnaires and other assessments should occur in the same week as planned. In the case of early discontinuation of treatment, all attempts will be made to collect the questionnaires until the end of the study.
2. ECOG Performance Status will be assessed  $\leq 28$  days before the consent.
3. The medication lists will include both prescription and non-prescription pain medication.
4. Patients will be monitored for side effects at each acupuncture and sham acupuncture session .
5. This will be performed by an IMS research study assistant who will go through training before the initiation of the study. A window of + 1 week applies to the baseline assessments, and a window of +/- 3 days applies to week 8 and week 12 assessments.
6. Can be performed over the phone.

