### **Acupuncture:**

Most common side effects (<5%):

- Very minor bleeding at acupuncture sites
- Bruises at acupuncture sites

- Minor pain or an unfamiliar sensation at acupuncture sites (local or radiating)

Less common side effects (<1%):

- Local allergic reaction (urticaria)
- Drowsiness, sleep disturbances (insomnia)
- Anxiety, nervousness
- Fainting, dizziness, nausea, vomiting (vasovagal reaction)

Rare but more serious side effects (<0.1%):

- Local skin infection

Severity will be graded as “serious” or non-serious.” Serious AEs are those that require hospitalization, lead to death or disability or require urgent medical attention to prevent death or disability. The intensity of non-serious AEs will be graded as mild, moderate or severe.

Causality will be assessed as follows. The AE will be described as "Probable" if all of the following apply: there is a rational relationship between the occurrence of the AE and the time of treatment; the AE has already been described as an AE of acupuncture or could reasonably be anticipated to be an acupuncture AE; regression or disappearance of the AE (unless permanent) after discontinuation of treatment or dose reduction; AE cannot plausibly be explained in terms of other causal factors. The AE will be described as "Possible" if all of the following apply: there is a rational relationship to the time of treatment administration; the AE has already been described as an AE of acupuncture; the AE could be explained by other factors. The AE will be described as "Improbable" if the following apply: there is no rational relationship to the time of treatment administration; the AE has not been reported so far as a side effect of treatment and cannot reasonably be expected as an acupuncture side-effect and any of the following: non-permanent AE persists after discontinuation of the treatment or dose reduction; repeated exposure does not lead to reappearance of the AE; AE could be explained by numerous other factors. The AE will be described as "No relationship" if all of the following apply: there is no rational relationship to the time of treatment administration; AE is evidently caused by other factors, e.g. symptom of a concomitant disease. The AE will be described as "Unable to evaluate" if the amount and content of data do not permit a judgment of the relationship to the treatment.

Quantitative Sensory Testing (QST): QST is not invasive and associated with no known risk.

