## **15.2 Randomization**

Randomization is implemented via MSKCC's Clinical Research Database (CRDB), a secure system that ensures that treatment allocation cannot be guessed before or modified after a patient is registered on trial, allowing for full allocation concealment. Randomization will be 1:1:1 (ACU:Sham: UC) using randomly permuted blocks of random length stratified by type of the most bothersome CIPN symptom (tingling vs numbness vs pain) and severity of such symptom (moderate 4-6 vs 7-10 on NRS). Once the patient is randomized, the CRS or CRM will inform the acupuncturist of the patient's group assignment and the RSA of whether the patient was assigned to an acupuncture group or to the UC group. The RSA's and patients will be blinded to which acupuncture group the patient was assigned. The acupuncturists will be the only ones unblinded. The rest of the study co-investigators and staff will remain blinded.

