### **17.2 Serious Adverse Event (SAE) Reporting**

An adverse event is considered serious if it results in ANY of the following outcomes:

- Death
- A life-threatening adverse event
- An adverse event that results in inpatient hospitalization or prolongation of existing hospitalization
- A persistent or significant incapacity or substantial disruption of the ability to conduct normal life functions
- A congenital anomaly/birth defect
- Important Medical Events (IME) that may not result in death, be life threatening, or require hospitalization may be considered serious when, based upon medical judgment, they may jeopardize the patient or subject and may require medical or surgical intervention to prevent one of the outcomes listed in this definition

Note: Hospital admission for a planned procedure/disease treatment is not considered an SAE.

SAE reporting is required as soon as the participant signs consent. SAE reporting is required for 30-days after the participant's last investigational treatment or intervention. Any events that occur after the 30-day period and that are at least possibly related to protocol treatment must be reported.

If an SAE requires submission to the IRB office per IRB SOP RR-408 'Reporting of Serious Adverse Events', the SAE report must be sent to the IRB within 5 calendar days of the event. SAE's classified as unrelated to the study intervention (per section 11.0) will not be

considered reportable to the IRB and will not have a corresponding Clinical Research Database (CRDB) SAE report generated). The IRB requires a Clinical Research Database (CRDB) SAE report be submitted electronically to the SAE Office as follows:

For IND/IDE trials: Reports that include a Grade 5 SAE should be sent to [[contact]](mailto:[contact]). All other reports should be sent to [[contact]](mailto:[contact]).

For all other trials: Reports that include a Grade 5 SAE should be sent to [[contact]](mailto:[contact]). All other reports should be sent to [[contact]](mailto:[contact]).

The report should contain the following information:

Fields populated from CRDB:

- Subject's initials
- Medical record number
- Disease/histology (if applicable)
- Protocol number and title

Data needing to be entered:

- The date the adverse event occurred
- The adverse event
- The grade of the event
- Relationship of the adverse event to the treatment (drug, device, or intervention)
- If the AE was expected
- The severity of the AE
- The intervention

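### Non-serious adverse events are recorded only if first judged related to acupuncture, possibly by the unblinded acupuncturist, with no routine collection specified for usual care and no safety assessment scheduled at week 12

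*Protocol*

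**What the plan says.** **Recording rule.** Section 11.0: "Only adverse effects related to the administration of acupuncture will be collected each week by the acupuncturist or research study assistant". The sentence before it says that side effects are monitored at every visit and names no arm.

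**Timing.** Section 9.0 says that acupuncture-related effects "will be collected each week before and after each treatment by the acupuncturist or research study assistant". Footnote 4 to the Safety Assessment row of Table 2 reads "Patients will be monitored for side effects at each acupuncture and sham acupuncture session". That row is ticked at baseline, week 4 and week 8, is blank at week 12, and is not split by arm.

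**Blinding.** Section 15.2: "The acupuncturists will be the only ones unblinded", and "The RSA's and patients will be blinded to which acupuncture group the patient was assigned". The RSA is told only whether a patient is in a needling arm or in usual care.

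**Causality.** Section 11.0 defines five levels: Probable, Possible, Improbable, No relationship and Unable to evaluate. One condition for No relationship is "AE is evidently caused by other factors, e.g. symptom of a concomitant disease".

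**Serious events.** Section 17.2 starts reporting at signed consent and adds "SAE reporting is required for 30-days after the participant's last investigational treatment or intervention". Serious events classed as unrelated under Section 11.0 are not reportable to the IRB and generate no database report. Section 11.0 has its own definition: "Serious AEs are those that require hospitalization, lead to death or disability or require urgent medical attention to prevent death or disability". Section 17.2 gives a different list.

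**The concern.** A causality scale is useful when events are captured first and attributed afterwards. Section 11.0 reverses that order for non-serious events: an event judged unrelated leaves no record, so the judgement cannot be reviewed or compared across arms later.

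Two comparisons suffer. Between real and sham, the person deciding what counts as related may know which treatment was given, and the protocol does not say whether that person or the blinded RSA decides. Against usual care, a patient who receives no acupuncture cannot have an effect related to receiving it. The rule therefore yields no usual care events, even if monitoring at every visit is read as covering all arms.

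This matters in a pilot because its purpose is to inform a definitive trial. The background section also weighs duloxetine partly on its side effects and calls for safe treatments. Information discarded before recording cannot be recovered when that trial is planned.

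**Working it through.** The protocol states no safety rate, power or sample size, so there is no figure to reproduce. The check sets the sections side by side and adds simple arithmetic.

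**1. Recording rule against causality scale.** If only related non-serious events are recorded, Improbable and No relationship have nothing to classify among them. Serious events differ: Section 17.2 takes them in from consent with no relatedness condition and then sorts them by the Section 11.0 scale. The conflict is therefore confined to non-serious events.

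**2. Who applies the filter.** Sections 9.0 and 11.0 name the same two alternative collectors. By Section 15.2 one is unblinded and the other is blinded to real versus sham. Nothing says which collects when, or how often.

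**3. Usual care.** Footnote 4 and Section 9.0 place collection at needling sessions. The usual care tasks in Sections 4.2 and 9.0 are sensory and pain-modulation testing, questionnaires and pain medication, with no adverse event item. Section 11.0 (every visit) and the unsplit Table 2 row point the other way. The text is contradictory, and no routine collection of non-serious events is spelled out for this arm.

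**4. Week 12.** Week 8 ends on day 8 × 7 = 56 and week 12 on day 12 × 7 = 84. With the last session at day 56, the serious-event window ends at 56 + 30 = day 86. Assuming instead that the last session can fall anywhere in week 8 (days 50 to 56), the window ends between day 80 and day 86. Either way it runs well past the last ticked safety assessment, and testing is scheduled for every arm at week 12. In usual care, the last treatment or intervention that anchors the window is not defined.

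**5. Two definitions of serious.** Section 17.2 lists life-threatening events, prolonged hospitalization, congenital anomaly and important medical events, and excludes planned admissions. Section 11.0 names none of these, although its urgent-attention clause overlaps with some.

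**6. What 25 per arm can show.** Section 11.0 gives side-effect frequencies only as upper limits: 5%, 1% and 0.1%.
- Chance of at least one event in an arm, 1 − (1 − p)^25: 72% at p = 5%, 22% at 1%, 2.5% at 0.1%.
- Expected events at 5%: 25 × 0.05 = 1.25.
- Weight of one event: 1/25 = 4 percentage points.
- Upper 95% bound after 0/25: 1 − 0.05^(1/25) = 11.3% one-sided; 1 − 0.025^(1/25) = 13.7% two-sided.
- Two-sided Fisher exact test against 0/25: 5/25 gives p = 0.0502; 6/25 gives p = 0.022.

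So even complete capture supports description only. With counts this small, a few differing decisions about relatedness can also change what is described.

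**The case against.** The best defence is that this is a small efficacy pilot with no between-arm safety objective or endpoint, that 25 per arm could never support more than description, and that serious events are covered in every arm from consent. All of that stands and limits how much weight the point can bear.

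Three stronger readings are tempting, and the documents do not support them:
- *Unblinded acupuncturists do the filtering.* The blinded RSA is named as an equal alternative. The defect is that the choice is left open.
- *The lower causality levels can never be used.* Section 17.2 uses the Section 11.0 scale to decide which serious events are reportable.
- *Nothing is collected in usual care or after week 8.* Serious events are reportable in both cases, later events that are at least possibly related must also be reported, and Section 11.0 speaks of monitoring at every visit.

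It is also fair to say that insomnia and anxiety, both listed as possible acupuncture effects, are measured in all arms by ISI and HADS at baseline and weeks 8 and 12, so usual care data on those two exist. Dizziness and nausea are listed as vasovagal reactions, for which usual care offers little natural comparison.

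None of this answers the core point. Small numbers limit precision; they do not justify deciding relatedness before recording, or leaving open whether the person who decides is blinded.

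**Conclusion.** The point holds in limited form and is worth correcting. As written, non-serious events are pre-filtered for relatedness by a collector whose blinding is not fixed, no routine collection of them is specified for usual care, and no safety assessment is scheduled at week 12. Descriptive rates are therefore open to ascertainment bias between real and sham, and non-serious events have no usual care reference.

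A reader might infer that the pilot cannot compare safety between arms at all. That goes too far: the two needling arms share one schedule and can be described side by side on related events, and serious events are reportable in all three arms.

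The size of the bias cannot be computed, because the protocol gives no background rates and does not say how often the acupuncturist would be the collector. The day 86 figure assumes a last session at the end of week 8.

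**What to change.** - Replace the Section 11.0 sentence so that all adverse events, regardless of cause, are recorded at each session and at the week 4, 8 and 12 contacts in all three arms.
- Name the collector. At weeks 4, 8 and 12 the RSA blinded to real versus sham asks every patient the same open question. Without this, the possible unblinded filter survives the edit.
- Assign causality with the existing Section 11.0 scale only after the event is recorded.
- Tick Safety Assessment at T3 in Table 2.
- Reconcile footnote 4, Section 9.0, Section 11.0 and Section 17.2 on arms and timing, including what ends the serious-event window in usual care, and reconcile the two definitions of serious.

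The contacts already exist in all arms, and week 4 in usual care can be by telephone. The cost is one question per contact, some wording, and a few more minor events to record and classify. The RSA will still know who is in usual care, so that comparison remains unblinded and descriptive.
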